### Data collection procedure

During the 2-year period from the start of the intervention, community eye camps will be offered once per year in each study ward. At screening camps, attendees will have their address documented, standardized ophthalmic examinations performed (visual acuity testing using a Snellen tumbling E chart, pinhole for those worse than 6/18, direct ophthalmoscope (arc light), and portable slit lamp examinations)

All individuals found at screening camps to have operable cataract (defined as BCVA worse than 6/36 in the better Seeing Eye with cataract as the probable primary cause for visual impairment) will be counselled about the option for surgery and given a written referral to the base hospital. Additional instructions and assistance will be given as per the co-created intervention package in the intervention arm. Community health workers (community eye champions) diaries will also be used to monitor implementation of the intervention and any other observation during implementation.

## Study masking

Community-led interventions are difficult to blind since the wards are already classified into controls and intervention. However, the study statistician and the data clerks at the base hospital will be masked as to whether the patient comes from an intervention or control ward.

## Data collection tools

All clinical data collected at screening camps will be captured in a standardized fashion, in real time using portable electronic devices running the CTO Survey data collection mobile app. The data will be backed up to a central, secure database at the end of each day. The database will be used to track individuals from study villages who were referred for cataract surgery and progression of implementation.

## Description of variables

### Outcomes variables

#### Primary outcome

The primary outcome will be the proportion of all eligible persons with operable cataract who accepted and show up for cataract surgery at the base hospital overall and stratified by age, sex, and VA levels. Based on the 2022 population census, the appropriate population of people aged 50 years and above will be sought from the ward authorities for denominator calculation.

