## Abstract

Age-related lens opacification (cataract) remains the leading cause of visual impairment and blindness worldwide. In low- and middle-income countries, utilization of cataract surgical services is often limited despite community-based outreach programmes. Community-led research, whereby researchers and community members collaboratively co-design intervention is an approach that ensures the interventions are locally relevant and that their implementation is feasible and socially accepted in the targeted contexts. Community-led interventions have the potential to increase cataract surgery uptake if done appropriately.

In this study, once the intervention is co-designed it will be implemented through a cluster-randomized controlled trial (cRCT) with ward as a unit of randomization.

This study will utilise both the qualitative methods for co-designing the intervention and the quantitative methods for effective assessment of the developed community-led intervention through a cRCT in 80 rural wards of Dodoma region, Tanzania (40 Intervention). The ‘intervention package’ will be developed through participatory community meetings and ongoing evaluation and modification of the intervention based on its impact on service utilization. Leask’s four stages of intervention co-creation will guide the development within Rifkin’s CHOICE framework. The primary outcomes are two: the number of patients attending eye disease screening camps, and the number of patients accepting cataract surgery. NVivo version 12 will be used for qualitative data analysis and Stata version 12 for quantitative data. Independent and paired t-tests will be performed to make comparisons between and within groups. P-values less than 0.05 will be considered statistically significant.

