### Study population and follow-up

Using data from the 2022 Tanzanian national census (accounting for predicted annual population growth of 2.7% up to the year 2023 for Dodoma region), we expect an average of 1420 adults aged 50 years and above in each study arm (coefficient of variation = 0.4).

Two years of follow-up will yield a mean of 2840 person-years of observation per intervention arm. Based on unpublished findings from a pilot study involving four wards conducted in 2020 by our research team we anticipate a screening rate (i.e. rate of presentation to screening camps among population >50 years of age) of 0.198 per person-year in control villages with an inter-village coefficient of variation (k) of 0.4. For cataract surgery, we anticipate a rate of 0.045 per person-year in control villages based on an estimated prevalence of visually significant cataract of 17.7%, and cataract surgical coverage of 25%. We conservatively assumed we would observe a level of inter-ward variation in surgery acceptance rates like that for screening rates (k = 0.4).

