#### Control wards

Control wards will receive the standard community eye screening routine package as it has been carried out, at a frequency of once per year. A comparison of the two arms is shown in Table 1.

**Table 1. bpae016-T1:** Comparison of the two arms of the study.

Item	Intervention arm	Control arm
Community sensitization	Yes	
	Local announcements method available: posters and announcement in churches, mosques, and schools.	
	*Additional community-determined sensitization methods*	N/A
Provision of eye diseases screening camp at a ward	A team composed of ophthalmologist/cataract surgeon, two ophthalmic nurses, optometrist, and outreach coordinator	
	*Intervention facilitator for continued intervention implementation*	NA
Referral from ward to base hospital for surgery	Yes, with the standard usual support	
	*Additional community-determined support to attend base hospital*	NA
Assessment of primary outcome	Same for both arms (trained field worker)	
Assessment of referrals	Outreach team	
	*Study coordinators follow up for non-attenders*	
Post-op care	Standard care as usual	
	*Qualitative study on reason for non-attendance*	NA

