### Eligibility and recruitment

#### Clusters/wards/individuals

All rural wards of Dodoma region are eligible to be selected. A total of 80 wards will be selected at random from the administrative list of all wards and randomized 1:1 to control and intervention arms. All adults 50 years of age or older who attend community eye outreach camps will be enrolled.

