#### Secondary outcomes

Proportion of all eligible persons attending at outreach eye examinations sites overall and stratified by age, sex, and VA levels (Screening rates)Acceptability, appropriateness, and fidelity of the community-led intervention. At study outset, distance of each study ward from the base hospital will be measured. Social economic status of each ward, Education levels, and economic activities of each ward will be obtained from the recent released National censors results.
*Acceptability* of the intervention will be assessed by using the standardized Acceptability of Intervention Measure questionnaires to evaluate the affective attitude, burden, perceived effectiveness, and ethicality of an intervention [35, 36].
*Appropriateness* will be assessed by using the Intervention Appropriateness Measure questionnaires to measure the perceived need, suitability, alignment, or compatibility of the intervention with the context, culture, or priorities of the participants and the research team [36].
*Fidelity* which is the extent to which the intervention is delivered or implemented as intended by community will be assessed using the Fidelity of Implementation Rating System checklist that evaluates the adherence, quality, and differentiation of an intervention delivery [37, 38].

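### The primary outcome is given two incompatible denominators; if the operable-cataract one is used, the comparison is open to selection and is not the quantity powered

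*Protocol article*

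**What the plan says.** The protocol article describes the surgery outcome in several forms.

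- **Primary outcome section, first sentence:** the "proportion of all eligible persons with operable cataract who accepted and show up for cataract surgery at the base hospital", overall and by age, sex and visual acuity (VA).
- **Primary outcome section, next sentence:** "the appropriate population of people aged 50 years and above will be sought from the ward authorities for denominator calculation".
- **Abstract:** "The primary outcomes are two: the number of patients attending eye disease screening camps, and the number of patients accepting cataract surgery". This is a count with no denominator.
- **Study population and follow-up:** "For cataract surgery, we anticipate a rate of 0.045 per person-year in control villages". The sample-size section carries this rate into a person-years formula.
- **Statistical analysis and data management:** a surgery acceptance rate is modelled, and no denominator is named.

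On who can be known to have operable cataract, the eligibility section says: "All adults 50 years of age or older who attend community eye outreach camps will be enrolled". The Data collection procedure section applies the definition to "All individuals found at screening camps to have operable cataract". No ward-wide survey of operable cataract is described. Camps run during the two years from the start of the intervention. Table 1 gives the intervention arm alone "Additional community-determined sensitization methods".

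The screening outcome is also to be split by VA: "Proportion of all eligible persons attending at outreach eye examinations sites overall and stratified by age, sex, and VA levels". The only VA measurement described is the one at camps.

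**The concern.** The two sentences of the Primary outcome section define different quantities. One asks what share of people with operable cataract came for surgery. The other divides by everyone aged 50 and above in the ward.

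The first denominator can be observed only among camp attendees. That group forms after randomisation, in an unmasked trial, through behaviour that the intervention is designed to change. Attenders in the two arms need not be alike, so a comparison restricted to them can differ between arms for reasons other than willingness to have surgery. It also misses surgeries gained by bringing more people to camp, which is half of what the intervention sets out to do.

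If the choice stays open until data are in hand, the same trial could report a clear gain or no effect depending on the definition used.

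**Working it through.** **1. What was powered.** The sample-size section uses the Hayes-Bennett formula for unmatched rates:

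c = 1 + (1.96 + 0.84)² × [(λ0 + λ1)/y + k²(λ0² + λ1²)] / (λ0 − λ1)²

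The inputs from the protocol are λ0 = 0.198 (screening) and 0.045 (surgery), λ1 = 1.3 × λ0, k = 0.4, and 1420 adults per ward, so y = 1420 person-years for one year or 2840 for two.

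| Outcome | y = 1420 | y = 2840 | Stated |
|---|---|---|---|
| Screening | 39.21, so 40 | 38.85, so 39 | 39 |
| Surgery | 41.63, so 42 | 40.06, so 41 | 42 |

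The stated figures match exactly at different values of y, but both come from rates over the whole population aged 50 and above. That is the powered quantity.

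**2. The two denominators differ in scale.** A rate of 0.045 per person aged 50 and above corresponds to 0.045/0.177 = 0.25 per person with cataract, at the protocol's 17.7% prevalence.

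**3. How each responds to the intervention.** For a ward with N adults aged 50 and above, attendance a, operable share among attendees s, and acceptance among operable attendees p:

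- surgeries = N × a × s × p
- population rate = a × s × p
- camp proportion = (N × a × s × p)/(N × a × s) = p

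The camp proportion does not contain a. If a rises by 30% with s and p unchanged, the population rate ratio is 1.30 (0.045 to 0.0585) and the camp proportion ratio is 1.00. This is algebra and holds for any baseline values.

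**4. If the added attendees are less willing.** Let their acceptance be r times that of the others, with the same operable share. For attendance × 1.3:

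- population rate ratio = 1 + 0.3r
- camp proportion ratio = (1 + 0.3r)/1.3

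| r (assumed) | Population rate ratio | Camp proportion ratio |
|---|---|---|
| 1.0 | 1.30 | 1.00 |
| 0.8 | 1.24 | 0.954 |
| 0.5 | 1.15 | 0.885 |
| 0.25 | 1.075 | 0.827 |

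For any r between 0 and 1 the ward rate rises while the proportion falls. The documents give no value for r.

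**5. VA strata.** Since VA is measured only at camps, residents who do not attend have none on record. A ward-population proportion within a VA level therefore has no denominator.

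**The case against.** The strongest reply is that the only sentence about calculating a denominator names the population aged 50 and above, in agreement with the sample size. On that reading no selection problem arises. Nor does it arise if operable cases are estimated as census population times a fixed prevalence. This stands, and it makes the bias conditional. It does not remove the contradiction: the defining sentence names persons with operable cataract, and the analysis section names no denominator. An analysis plan not shown may choose, but the protocol's own text would still conflict.

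It is also fair that the ratio of 1.00 assumes no effect on acceptance. Table 1 gives the intervention arm extra support to reach the base hospital, so acceptance may rise. The camp proportion would then show that part of the effect and still miss the part that comes through attendance.

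A reader might infer more than the documents support:

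- **That an effective intervention will look harmful.** This needs the operable-cataract denominator and less willing newcomers. The second is an assumption.
- **That 40 wards per arm are too few for the proportion.** Taking 17.7% of attendees as operable and 25% as accepting suggests this, but it implies 0.198 × 0.177 × 0.25 = 0.0088 surgeries per person-year against the stated 0.045. Matching 0.045 gives 0.045 × 2840 = 127.8 surgeries per ward. The corresponding formula for proportions then gives 39.1 (50% versus 65%, 255.6 operable per ward) or 39.6 (25% versus 32.5%, 511 per ward), so 40 wards in each case.
- **That intention-to-treat is abandoned.** Wards are analysed as randomised; the issue is which quantity is compared.
- **That the numerator takes every camp attendee.** It counts people who come for surgery. Addresses are recorded and referrals from study villages are tracked.
- **That ward authorities' figures compete with the census.** The protocol ties that denominator to the 2022 census.

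**Conclusion.** The concern holds in conditional form. The protocol gives its primary outcome two incompatible denominators, uses a count in the abstract, and powers a population rate. If the operable-cataract denominator is used, the comparison is open to selection by attendance and is not the quantity powered.

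The firm result is 1.30 against 1.00, for a 30% rise in attendance with the same operable share and acceptance. The opposite-direction results, such as 1.15 against 0.885, rest on assumed lower willingness among added attendees and show only what is possible. With the census denominator the problem disappears, so the defect is that the protocol leaves the choice open on its primary outcome.

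**What to change.** Define one primary outcome that matches the sample size: the number of ward residents aged 50 and above who were referred from camps and who present for cataract surgery at the base hospital over the two years, divided by person-years of the ward's census-based population of that age. Residence comes from the recorded address and the referral tracking. Use the same population source in both arms.

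State the limit of that numerator. Residents who reach hospital without a camp referral can be counted only if the hospital records their ward, which the protocol does not show. If they are to be included, a ward-of-residence field at the hospital is needed in both arms. If they are not, confirm that 0.045 is the expected control rate for camp referrals alone, since it implies 0.045/0.198 = 0.227 surgeries per camp attendance.

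Make the proportion among camp-detected operable cataract a descriptive secondary outcome. Limit VA stratification to descriptions of attendees. Align the abstract and the statistical analysis section with the chosen definition.

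The cost is wording, plus one data item if non-referred residents are counted. The sample size need not be redone on account of this change, because the population rate is what it already uses.

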#### Secondary outcomes

Proportion of all eligible persons attending at outreach eye examinations sites overall and stratified by age, sex, and VA levels (Screening rates)Acceptability, appropriateness, and fidelity of the community-led intervention. At study outset, distance of each study ward from the base hospital will be measured. Social economic status of each ward, Education levels, and economic activities of each ward will be obtained from the recent released National censors results.
*Acceptability* of the intervention will be assessed by using the standardized Acceptability of Intervention Measure questionnaires to evaluate the affective attitude, burden, perceived effectiveness, and ethicality of an intervention [35, 36].
*Appropriateness* will be assessed by using the Intervention Appropriateness Measure questionnaires to measure the perceived need, suitability, alignment, or compatibility of the intervention with the context, culture, or priorities of the participants and the research team [36].
*Fidelity* which is the extent to which the intervention is delivered or implemented as intended by community will be assessed using the Fidelity of Implementation Rating System checklist that evaluates the adherence, quality, and differentiation of an intervention delivery [37, 38].

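### A screening proportion within each visual acuity level cannot be computed, because acuity is measured only in people who attend the camps

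*Protocol article*

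**What the plan says.** All places are in the protocol article.

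- **Outcome.** Secondary outcomes lists "Proportion of all eligible persons attending at outreach eye examinations sites overall and stratified by age, sex, and VA levels (Screening rates". Acuity stands beside age and sex as a stratifying factor.
- **Population basis.** Study population and follow-up describes the screening rate as the "rate of presentation to screening camps among population >50 years of age", that is, among all older residents and not among attendees.
- **Denominator.** Primary outcome states, with reference to the 2022 census, that "the appropriate population of people aged 50 years and above will be sought from the ward authorities for denominator calculation". No other denominator source is named.
- **Where acuity is measured.** Data collection procedure: "At screening camps, attendees will have their address documented, standardized ophthalmic examinations performed (visual acuity testing using a Snellen tumbling E chart".
- **Who is enrolled.** Clusters/wards/individuals: "All adults 50 years of age or older who attend community eye outreach camps will be enrolled".
- **Other ward-level data.** Secondary outcomes adds distance from the base hospital and "Social economic status of each ward, Education levels, and economic activities of each ward will be obtained from the recent released National censors results". None of these is acuity.

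**The concern.** A proportion stratified by a factor normally has that factor in both numerator and denominator. For age and sex this is feasible, because a population count can be split by age and sex. For acuity it is not, because a resident's acuity becomes known only when that resident attends. The numerator within a band is observed; the denominator is not.

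The breakdown bears on whether a package meant to raise cataract surgery uptake draws in people with poor sight or simply more people. If the analyst meets the problem at the end of the trial, the likely substitute is the acuity mix among attendees. Reported under the label of screening rates, that mix could mislead: the impaired share of attendees rises if more impaired people come, but also if fewer well-sighted people come. The Abstract names camp attendance as one of two primary outcomes and the sample size section powers it as outcome 1, so a breakdown of it is likely to be read with attention.

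**Working it through.** **1. Inputs.** Control screening rate "of 0.198 per person-year in control villages" (Study population and follow-up); 1420 adults per ward, k = 0.4, a 30% increase, and z values 1.96 and 0.84 (Sample size, randomization, and allocation concealment); 2840 person-years over two years (Study population and follow-up). That last section attaches 1420 to the study arm, whereas the sample size section attaches it to the ward. I read it as per ward. The percentages below do not depend on this.

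**2. The plan's own figure.** With λ0 = 0.198, λ1 = 1.3 × 0.198 = 0.2574 and y = 2840:

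c = 1 + (1.96 + 0.84)² × [(0.198 + 0.2574)/2840 + 0.16 × (0.198² + 0.2574²)] / 0.0594² = 38.85

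The protocol states 39. This confirms that 0.198 is used as a rate over the whole older population. It has no further bearing on the point.

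**3. Tracing numerator and denominator.**

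| Quantity | Numerator | Denominator | Computable? |
|---|---|---|---|
| Overall proportion | Attendees | Ward count aged 50+ | Yes |
| Within age or sex | Attendees by age, sex | Ward count by age, sex | Yes, if counts are obtained by age and sex |
| Within acuity level | Attendees by acuity | Residents by acuity | No source |
| Acuity band over all residents | Attendees by acuity | Ward count aged 50+ | Yes |

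Other passages do not fill the gap. The rapid-assessment survey from nearby regions is used only to guide interview questions (Conducting stage). The 17.7% prevalence serves only as a planning assumption for the surgery rate. The follow-up of non-attenders in Table 1 sits under assessment of referrals, so it appears to concern people already examined at a camp. The multiple imputation in Statistical analysis and data management cannot help: people who never attend are not enrolled and have no individual record.

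**4. Share without an acuity measurement, control arm.**

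- One year: attendees 0.198 × 1420 = 281; not measured 1420 − 281 = 1139, or 80%.
- Two years, nobody attends twice (assumption): 1420 − 2 × 281.16 = 858, or 60%.
- Two years, the same people attend both times (assumption): 1139, or 80%.
- Intervention arm at the target effect, one year: 1 − 0.2574 = 74%.

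**5. What the missing denominator does.** Suppose that 30% of the 281 attendees are visually impaired (assumption): 84.3 people. The screening rate in the impaired stratum is 84.3 / (1420 × prevalence):

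| Ward prevalence of impairment (assumed) | Residents impaired | Stratum rate |
|---|---|---|
| 25% | 355.0 | 0.24 |
| 17.7% | 251.3 | 0.34 |
| 10% | 142.0 | 0.59 |
| 5% | 71.0 | 1.19 (impossible with one attendance per person) |

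The observed camp data would be the same in the first three rows. The planned data cannot tell those three apart.

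**The case against.** The strongest counter-argument is that the outcome sentence gives no stratum-specific denominator. Its words also allow attendees in each acuity band divided by all eligible persons. That quantity can be computed and is what the fix below asks for. On that reading the defect is one of wording. This stands in part, and it is why the point is not that every reading fails. But acuity is listed beside age and sex, where stratification naturally means stratum-specific denominators, so the sentence still has to change.

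A second argument is that this is a condensed article, and tabulation detail belongs in the analysis plan. An analysis plan could choose the denominator. It could not create acuity data for people who were never examined, so the natural reading is a stated analysis that the data cannot deliver, not an omitted detail.

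Third, the breakdown is secondary, the objectives state no acuity-specific hypothesis, and the power calculation covers overall rates only. This is correct and limits the weight of the point.

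A reader might also infer that every stratum would come out at 100% because only attendees are enrolled. The documents do not support that: the screening rate is defined over the whole older population, and the denominator is the ward count. Nor is 80% a trial-wide figure for missing acuity. It is one year in the control arm, and it describes coverage, not bias.

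**Conclusion.** The point holds for the acuity strata of the screening proportion, on the natural reading of the outcome. No planned source gives the number of residents at each acuity level. In the control arm about 80% of residents aged 50 and above are unmeasured in one year, and about 60% to 80% over two annual camps. These figures assume 0.198 per person-year, at most one attendance per person per camp, and repeat attendance anywhere between none and complete.

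It would be tempting to conclude that the screening outcome as a whole lacks a denominator. The documents do not support this. The overall proportion, the sample size and the surgery outcome do not depend on the acuity breakdown, and the age and sex strata need only ward counts split by age and sex. The protocol names a count aged 50 and above without saying whether it will be split. The stratum rates in the last table rest on assumed shares and prevalences; they show only that the quantity is not identified.

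**What to change.** In Secondary outcomes, remove acuity from the strata of the screening proportion and keep age and sex, stating that the ward counts will be obtained by age and sex. Add a separate descriptive item: by arm, attendees in each acuity band per 1000 ward residents aged 50 and above, with the full count as denominator in every band. Name the bands, and state that this is not a screening rate within acuity level.

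Compare arms with whatever ward-level method is used for the overall screening outcome. The statistical section names t-tests or Wilcoxon tests for differences between arms and states mixed-effects modelling only for surgery acceptance, so the item should not presuppose a rate-ratio model for screening.

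The comparison is informative because the per-1000 figure in a band equals 1000 × (band prevalence) × (attendance within the band). Randomisation makes band prevalence equal between arms in expectation, so a between-arm difference reflects attendance, scaled by the unknown prevalence.

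The cost is a sentence or two and no new data on acuity. The downsides are small: a few extra descriptive comparisons, exposure to chance imbalance in the wards' acuity distribution, and a possible shift in that distribution in year 2 if surgery in year 1 differs between arms. Reporting the two years separately would show the last of these.
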